## 1. PROTOCOL SUMMARY

| **Title:** | Biofunctional textiles in the management of atopic dermatitis |
| --- | --- |
| **Précis:** | Atopic dermatitis (AD) is a chronic inflammatory skin disease characterized by exacerbations and remission of intensely pruritic lesions of variable location. AD may be acute (short-term and severe) with predominantly redness, vesicles and oozing, or it may be chronic (long-term) with scaling, skin thickening, altered pigmentation and exaggerated surface markings. The condition affects mainly the creases of the elbows and knees, and the face and neck, although it can affect any part of the body. The severity of AD is variable, ranging from localized mild scaling to generalized involvement of the whole body. Itching is the predominant symptom which can induce a vicious cycle of scratching, leading to skin damage. There is a tendency to lifelong dry sensitive skin. Skin of AD is often colonized by Staphylococcus aureus contributing to perpetuating cutaneous inflammation. AD treatment is based on skin hydration, identification and elimination of flare factors, and pharmacologic therapy. Biofunctional textiles are emerging as new and complementary tools . Chitosan is a natural polysaccharide with in vitro anti-microbial activity and regenerating properties. We aim to evaluate the effect of a textile coated with chitosan in management of AD as well as its impact on systemic inflammation and skin flora namely on colonization by Staphylococcus aureus .  Patients with medical diagnosis of AD are selected. Clinical data are collected and written information is provided. After enrollment patients are randomized to active group (cotton textiles impregnated with chitosan) or control group (cotton textiles). Patients are asked to use a Tshirt and pants as pijamas for a period of 8 weeks. Outcomes are clinical improvement measured by SCORAD (severity score of AD including subjective symptoms as sleep disturbance and pruritus and intensity and severity of skin lesions), quality of life, inflammatory serum markers and skin microbiological assays. |
| **Objectives:** | To assess the efficacy of a natural biopolymer textile in the management of atopic dermatitis, and to characterize its immunomodulatory properties and impact on skin microbiological flora . |
| **Setting:** | Immunology Department, Medical Faculty , Porto University |
| **Subjects:** | Portuguese patients, of any gender and any race, aged over 12 years old; |
| **Study design:** | Randomized, double-blind, parallel placebo-controlled study |
| **Estimated time to complete enrollment:** | 6 months |

## 2. Introduction: Background Information and Scientific Rationale

### 2.1 Background Information and Rationale

Atopic dermatitis (AD) is a chronic inflammatory skin disease characterized by exacerbations and remission of intensely pruritic lesions of variable location. It affects predominantly children but when persisting in adolescence and adulthood tends to be more severe (1). Studies in the first half of the twentieth century have shown an incidence of 2%–3% (2), while more recent surveys have shown an increase to 9%–12% in childhood (3). Its prevalence has been found unevenly distributed over the world and in Portugal, eczema prevalence was found to be 9.3 % and 5.2% on 6-7 and 13-14 years old respectively (4).

Atopic dermatitis has a significant impact on the quality-of-life of patients and their families, comparable to other chronic diseases, and its economic impact is high (5). More than 50% of patients with AD develop asthma and other atopic disorders, adding further impact in the health and economic burden of this disease.

Its pathogenesis is not fully understood and the interaction of environment in genetic predisposed individuals seems to be determinant(4) .Besides the involvement of adaptive immunes response trough mechanisms related to IgE synthesis, structural changes of the epidermis and innate immunity dysfunction play a significant role. Patients with fillagrin (a key protein of epidermal differentiation) gene mutation, comprise not only an earlier onset of disease as well as more severe and persistent AD (5, 6). AD patients also have an increased risk of infection with certain types of microorganisms (7) that has been related to immune deficiency of innate immune system on a already disrupted skin barrier.

AD may be acute (short-term and severe) with predominantly redness, vesicles and oozing, or it may be chronic (long-term) with scaling, skin thickening, altered pigmentation and exaggerated surface markings. The condition affects mainly the creases of the elbows and knees, and the face and neck, although it can affect any part of the body. The severity of AD is variable, ranging from localized mild scaling to generalized involvement of the whole body, with redness, oozing and secondary infection. Itching is the predominant symptom which can induce a vicious cycle of scratching, leading to skin damage which in turn leads to more itching - the so called “itch scratch itch” cycle. There is a tendency to lifelong dry sensitive skin.

There is currently no cure for AD however, a wide range of treatments are employed to control symptoms (9). Emollients and topical corticosteroids are universally recommended (10) and anti-histamines, topical tacrolimus and pimecrolimus are part of pharmacological options. Probiotics, and allergen immunotherapy are used as immunomodulators with controversial effectiveness

(11). Special textiles that can contribute to preserve skin integrity, prevent loss of water and exert immunomodulatory effects are being developed as complementary tools.

The concept of “biofunctional textiles” refers to the potential ability of certain textiles to modulate skin dryness, flora and/or immune status if they are used long enough and in close contact with skin. With the development of nanotechnology it became possible to impregnate textiles with bioactive compounds. Chitosan, a natural biopolymer has antioxidant, antibacterial and antifungal properties enhancing skin repair (8).

The clinical utility of textiles impregnated with chitosan in patients with AD has never been tested.

### 2.2 Potential Risks and Benefits

##### 2.2.1 Potential Risks

Chitosan is a linear polysaccharide derived from chitin. Chitin is the second most abundant natural polymer obtained from the exoskeleton of crustaceans. It has high biocompatibility and biodegradability with various applications in the pharmaceutical industry, which includes wound dressings, gauzes, and medical sutures and also in regenerative medicine. We do not expect to have adverse events related to the use of textiles coated with chitosan. Textiles will be made of smooth cotton fiber with appropriated manufacture for patients with skin diseases (no dyes, no preservatives with sensitization potential).

##### 2.2.2. Known Potential Benefits

Chitosan possesses various biological activities (antioxidant, wound-healing accelerator, antibacterial and antifungal). It has also been investigated as scaffold for skin regeneration due to its biocompatibility, biodegradability, and bioactivity.

## 3. Objectives

### 3.1 Study Objectives

To assess the efficacy of a natural biopolymer textile in the management of atopic dermatitis

### 3.2 Study Outcome Measures

##### 3.2.1 Primary Outcome

- Investigator rated eczema severity

Clinical improvement measured by local SCORAD (score of severity of AD- supplement 1) (initial versus final, % of change).

SCORAD is composed of three different domains (A= extension B= intensity C = subjective symptoms). To determine extent, the sites affected by eczema are shaded on a drawing of a body. The rule of 9 is used to calculate the affected area (A) as a percentage of the whole body: Head and neck 9% Upper limbs 9% each , Lower limbs 18% each , Anterior trunk 18% ,Back 18% 1% each for genitals, each palm and the back of each hand. The score for each area is added up. The total area is 'A', which has a possible maximum of 100%.

A representative area of eczema is selected. In this area, the intensity of each of the following signs is assessed as none (0), mild (1), moderate (2) or severe (3).:Redness ,Swelling ,Oozing / crusting Scratch marks , Skin thickening (lichenification),Dryness (this is assessed in an area where there is no inflammation) .The intensity scores are added together to give 'B' (maximum 18).

Subjective symptoms i.e., itch and sleeplessness, are each scored by the patient or relative using a visual analogue scale where 0 is no itch (or no sleeplessness) and 10 is the worst imaginable itch (or sleeplessness). These scores are added to give 'C' (maximum 20).

- Changes in Quality of life.

Patients are asked to answer the Portuguese version of the Dermatology Life Quality Index (> 16 years old) or the children´s Dermatology Quality of Life Index (4-16 years old) at the beginning and end of the study (supplement 2 and 3)

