## 5. Study Enrollment and Withdrawal

### 5.1 Subject Inclusion Criteria

In order to be eligible to participate in this study, a subject must meet all of the following criteria:

- Medical diagnosis of atopic dermatitis
- Age superior to three years old

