### 8.2 Sample Size Considerations

Considering a parallel trial with a significant level of 0.05 and statiscal power of 0.8 based on difference of means and standard deviation of outcome SCORAD the sample size calculated was 90 patients

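### The SCORAD primary outcome is a percent change with no minimum baseline: undefined at zero, unstable at low scores, often less powerful than a baseline-adjusted final score, and not matched to a scale in the sample size section

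*Protocol*

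**What the plan says.** Section 3.2.1 of the protocol gives the SCORAD primary outcome as "Clinical improvement measured by local SCORAD (score of severity of AD- supplement 1) (initial versus final, % of change". It lists "Changes in Quality of life" as a second measure under the same heading.

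Section 5.1 has two inclusion criteria: "Medical diagnosis of atopic dermatitis" and "Age superior to three years old". Neither concerns severity, and no section requires active disease or a minimum score at Visit 1. Section 2.1 describes a disease that remits and relapses: "The severity of AD is variable, ranging from localized mild scaling to generalized involvement of the whole body".

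The score has no positive floor. In 3.2.1 "the intensity of each of the following signs is assessed as none (0), mild (1), moderate (2) or severe (3", the two symptom scales also start at 0, and extent is a sum of affected areas.

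Section 8.2 begins "Considering a parallel trial with a significant level of 0.05 and statiscal power of 0.8" and continues "based on difference of means and standard deviation of outcome SCORAD the sample size calculated was 90 patients". It gives no difference, no SD and no scale.

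**The concern.** A percent change divides by the patient's own baseline. At 0 it does not exist. Close to 0, an ordinary fluctuation of a few points becomes a change of several hundred percent. Worsening has no practical ceiling on this scale, whereas improvement stops at -100%, so the distribution is skewed towards the patients with least disease. The protocol admits such patients, and section 5.3 recruits from general practice and through media advertising, so mild cases are foreseeable.

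Two things are at stake. The first is the primary comparison: a handful of mild patients can move an arm mean and inflate its variance, although they say little about whether the textile works. The second is the power statement: 8.2 promises 80% power without saying for which form of SCORAD, so a reader cannot tell whether the promise covers the endpoint in 3.2.1.

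**Working it through.** **1. The plan's figure.** The inputs from 8.2 are alpha 0.05, power 0.80 and 90 patients. Two-sided testing, 1:1 allocation (45 per arm) and no dropout are assumptions. Without a difference and an SD, 90 cannot be reproduced forwards. Solved backwards:

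d = (1.960 + 0.842) × √(2/45) = 2.802 × 0.2108 = 0.591 SD.

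One-sided, d is 0.524. With 10%, 15% or 20% dropout (two-sided), it is 0.623, 0.641 or 0.660. On the score scale, 0.591 SD is 5.9 points if the SD is 10, 8.9 if 15 and 11.8 if 20. It could equally be 0.591 SD of percent change. The standardized figure fits any scale, so it cannot show which quantity was sized.

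**2. How one low baseline acts.** Invented values, for illustration only:

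- Baseline 50, final 40: (40 - 50)/50 = -20%.
- Baseline 5, final 20: (20 - 5)/5 = +300%.
- An arm of 45 with 44 patients at -20% and one at +300% has mean (44 × -20 + 300)/45 = -12.9%.

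One mild patient moves the arm mean by about 7 percentage points.

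**3. Power under a linear additive model.** Assumed: gamma baseline, mean 35, SD 18; final score linear in baseline; additive effect of 0.597 SD, which gives a t-test on the final score 80% power at 45 per arm (t-based; the normal approximation gives 0.591).

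| Baseline-final correlation | t-test on percent change | ANCOVA on final score |
| --- | --- | --- |
| 0.5 | about 70% | about 90% |
| range over 0.4 to 0.7 | 60-89% | 85-97% |

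The typical largest single percent change per simulated trial was +228% to +370% across these correlations.

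**4. Role of the missing minimum.** A separate simulation assumed baseline mean 30 to 45, SD 15, correlation 0.4 or 0.6 and an additive effect of 0.591 SD.

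| Minimum baseline | Percent change | ANCOVA |
| --- | --- | --- |
| none in practice (0.5) | 0.61-0.86 | 0.84-0.93 |
| 25 | 0.77-0.92 | 0.85-0.94 |

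Without a minimum the loss is about 7 points (0.929 - 0.860; mean 45, correlation 0.6) to 23 points (0.842 - 0.609; mean 30, correlation 0.4). Much of it goes once low baselines are excluded.

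**5. Other data models.**

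- Gamma margins at both visits, joined by a Gaussian copula, mean 35, SD 18, additive effect: at correlation 0.4, percent change 75% and ANCOVA 85%; at 0.5, 85% and 88-89%; at 0.7, 99% and 97%.
- Proportional effect (26% lower geometric mean, since exp(-0.3) = 0.74), no minimum: percent change 0.75-0.76 and ANCOVA 0.68-0.74.
- Another proportional-effect model, correlation 0.5: percent change 65% and ANCOVA 88%.

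The sign and size of the gap therefore depend on how scores and effect behave, which the protocol does not tell us.

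**The case against.** The strongest reply is that the power argument rests on inputs the protocol does not contain. Calibrating the effect on the final score presupposes that scale; had the 90 been sized on percent change, its power would be 80% by construction. The protocol names no test, and the analysis model may sit in an analysis plan that is not shown. In the copula model at correlation 0.5, a rank test on percent change reached 94%, above ANCOVA. All of this stands, and it makes the power loss conditional.

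It can also be said that near-zero baselines will be rare. SCORAD scoring in 3.2.1 presumes a representative area of eczema, and dryness is scored on uninflamed skin. Under the assumed gamma with mean 35 and SD 18, only 0.4% of baselines fall below 5 (about 0.3 of 90 patients) and 3.3% below 10 (about 3 of 90). A true zero is thus unlikely. But about three low baselines are enough for the extreme values shown above, and no rule in the protocol deals with them.

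Two stronger readings are tempting and are not supported. A reader might infer that the 90 patients were sized on a different quantity from the endpoint. Section 8.2 speaks only of outcome SCORAD, and a percent change also has a mean and an SD, so this could be the same quantity. A reader might also take the initial-versus-final wording in 3.2.1 as a within-patient test in place of a comparison of arms. It more naturally defines the change score, and the protocol summary, section 4 and section 8.2 all describe a parallel trial.

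What the reply leaves untouched is the metric. Percent change is fixed in the protocol itself, so a later analysis plan would inherit it.

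**Conclusion.** The point holds in a limited form and should be fixed. It follows from the protocol text alone that the SCORAD primary outcome is a ratio to a baseline with no lower limit, undefined at 0 and unstable at low values.

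The power cost is usual but not certain. It is about 7 to 23 points in one set of linear additive scenarios, and about 20 points (70% against 90%) at mean 35, SD 18 and correlation 0.5. It shrinks or reverses under some other models. These figures rest on assumed means, SDs, correlations and effect shapes, 1:1 allocation, no dropout and a t-test on percent change. Percent change is not always underpowered: with mean 45, SD 15 and correlation 0.6 it reached 86%, above the 80% in 8.2.

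On sample size, the supportable conclusion is that 8.2 cannot be matched to the endpoint in 3.2.1, not that it contradicts it.

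**What to change.** - In 3.2.1, define the SCORAD primary outcome as (local) SCORAD at Visit 2 (week 8), compared between chitosan and control by ANCOVA with Visit 1 SCORAD as covariate, and report the adjusted mean difference with its 95% CI. Use the same form of SCORAD, local or total, at both visits.
- Keep percent change as a descriptive summary.
- In 8.2, state the scale, the difference and the SD behind the 90 patients. If they were for percent change or absolute change, redo the calculation for the new quantity.

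Section 7 already records SCORAD at Visits 1 and 2, so no new visit or measurement is needed. The change to 3.2.1 is wording. The change to 8.2 needs the sponsor to retrieve or justify figures that the protocol does not print. The price is that the result is no longer headlined as a percent improvement, and the gain in power is not guaranteed under every data model. The change concerns SCORAD only; it does not settle the place of quality of life, which 3.2.1 also lists as primary.

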## 4. Study Design

Double blind, placebo-controlled, parallel randomized study enrolling a sample of patients with medical diagnosis of AD.

The approximate time to complete study enrollment is about 6 months. The expected duration of subject participation is eight weeks, approximately, with one screening visit and two visits after enrollment, one at the beginning and the other at end of the study. During the eight weeks trial the patient will be asked to use cotton Tshirt and cotton pants as pijama during the night.

Visits are performed at an appropriate medical setting at Instituto Cuf, Porto. Each visit lasts approximately 45 min including medical examination, filling of one questionnaire, serum sampling and a superficial skin swab of determined areas.

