## 7. Study Schedule

Visit 0:

- Explain study protocol
- Review medical history to determine eligibility based on inclusion/exclusion criteria.
- Schedule visit 1

Visit 1 :

- Provide written information about the study
- Obtain signature of potential subject on written informed consent
- Perform medical examination and register SCORAD index
- Answer a quality of life questionnaire
- Patients are explained and given a diary symptoms card
- Perform skin swab of determined areas
- Perform serum sampling
- Patients are explained trial and are given a TShirt and pants
- Surveillance and medical care, if required

Visit 2 :

- Review medical history including medications history
- Perform medical examination and register SCORAD index
- Answer a quality of life questionnaire
- Deliver the diary symptoms card
- Perform skin swab of determined areas
- Perform serum sampling

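### Section 3.2.1 calls the primary outcome a local SCORAD but describes a whole-body score with no fixed site for intensity, and its area weights add to 104% against a stated maximum of 100%

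*Protocol*

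**What the plan says.** Section 3.2.1 defines the first primary outcome as "Clinical improvement measured by local SCORAD (score of severity of AD- supplement 1) (initial versus final, % of change"). It does not define *local*. It then describes three domains.

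- **A, extent.** "The rule of 9 is used to calculate the affected area (A) as a percentage of the whole body". The weights are "Head and neck 9% Upper limbs 9% each , Lower limbs 18% each", then 18% each for the front of the trunk and the back, and "1% each for genitals, each palm and the back of each hand". The area scores are to be summed to give A, "which has a possible maximum of 100" per cent.
- **B, intensity.** "A representative area of eczema is selected", and six signs are graded there, except that dryness is graded on uninflamed skin.
- **C, symptoms.** Itch and sleeplessness are each rated 0 to 10, with no body site.

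Section 7 has the investigator, at Visit 1 and again at Visit 2, "Perform medical examination and register SCORAD index". The Section 1 summary and the sample-size statement in Section 8.2 say SCORAD, also without *local*. On the intervention, Section 4 says "During the eight weeks trial the patient will be asked to use cotton Tshirt and cotton pants as pijama during the night". Sections 1 and 2.1 list the face and neck among the main sites of disease.

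**The concern.** The product acts, if it acts, largely where cloth meets skin, and Section 2.1 describes biofunctional textiles as needing close contact. A score restricted to the garment area and a score over the whole body are therefore different endpoints that could give different answers. Two assessors following Section 3.2.1 in good faith could record different values for the same patient. A later analysis plan could not repair that, because the sites are chosen at the visit.

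The unfixed site for B is a second problem. The outcome is a change between two visits. If B is taken at one site at Visit 1 and another at Visit 2, part of the change reflects the choice of site. With random allocation and blinded assessment this adds noise rather than favouring an arm.

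The area weights are a plain scoring error: following the instruction to add them can give a value above the maximum that the same section states.

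**Working it through.** **1. Which score is meant?** Setting the places side by side:

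| Place in the protocol | What it implies |
|---|---|
| 3.2.1, name of the outcome | local, undefined |
| 3.2.1, A | whole body, including head, neck and hands |
| 3.2.1, B | one area; any site; no rule for the second visit |
| 3.2.1, C | no site |
| 1 and 8.2 | SCORAD |
| 7 | SCORAD index |

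Only the single word in the name points to a restricted area. None of the three domains is described as local. The description is exactly whole-body for A only; B is one area and C has no site.

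**2. Area weights.** Inputs are the weights in 3.2.1, and the rule is a simple sum.

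- Head and neck: 9
- Upper limbs: 2 × 9 = 18
- Lower limbs: 2 × 18 = 36
- Front of trunk and back: 18 + 18 = 36
- Subtotal: 9 + 18 + 36 + 36 = 99
- Genitals: 99 + 1 = 100
- Palms and backs of hands: 2 × 1 + 2 × 1 = 4, giving 100 + 4 = **104**

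The stated maximum of 100 is not reproduced. It is reproduced if the four hand items are treated as parts of the upper limbs and not added again (104 − 4 = 100). Reading the text as 1% per hand, palm and back together, gives 102. Dropping all the 1% items gives 99. Only nesting the hand items matches the stated maximum, and the text does not say to nest them.

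**3. How much of A lies outside the garment?** Sleeve length is not stated, so this is a range under assumption, with the feet counted as covered.

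- Long sleeves: head and neck 9 + hands 4 = 13 points, which is 13/104 = 12.5% as written, or 13/100 = 13% if the hands are nested.
- No part of the upper limb covered: 9 + 18 + 4 = 31 points, 31/104 = 29.8% as written, or 9 + 18 = 27 of 100 if nested.

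**4. Can a loss of power be stated?** Section 8.2 gives a 0.05 significance level, 0.8 power and 90 patients, but no difference, standard deviation, sidedness or allocation ratio. Assuming 45 per arm, a two-sided t test and no dropout, 80% power corresponds to a standardized effect d = 0.597. Suppose B is scored on uncovered skin in a fraction f of patients, the garment has no effect there, and B carries a share s of the total effect. The effect becomes d × (1 − s × f), and noncentral t power is:

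| s (assumed) | f = 10% | f = 25% | f = 40% |
|---|---|---|---|
| 1 (worst case) | 71% | 56% | 39% |
| 1/2 | 76% | 69% | 61% |
| 1/3 | 77% | 73% | 68% |

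Every input to this table except the significance level, the power and the total of 90 is assumed, so it illustrates sensitivity and does not estimate a loss.

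**The case against.** Whole-body SCORAD is a defensible primary outcome. The objective in Section 3.1 is management of atopic dermatitis, not of covered skin. Section 8.1 predicts lower inflammatory biomarkers, and Section 3.2.2 measures serum markers, so an effect beyond the garment is part of the hypothesis. This stands. The defect is that the protocol names one score and describes another.

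A reader might infer that scoring uncovered skin cuts power from 80% to as little as 39%. The documents do not support that. The figure requires B to carry the whole effect, although A and C also contribute. It rests on an effect size solved backwards from 90 patients, and it assumes no benefit away from the cloth. If the unstated planning figures came from ordinary whole-body SCORAD, any dilution is already in them and nothing is lost from 80%.

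A reader might also infer that, because the name says local, garment-only scoring must become primary. That rests on one undefined word against the whole scoring description, and it brings its own trouble. Section 5.1 does not require lesions on covered skin, so percent change would be unstable where the covered-skin baseline is near zero. C cannot be assigned to a site as it is described.

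On the weights, the error touches A only, applies alike to both arms, and needs hand involvement, which the hand-eczema exclusion in Section 5.2 probably makes less common. It is minor, but it is still a wrong rule in the primary outcome. Finally, the SCORAD form cited as Supplement 1 is not shown and may fix the site for B or define the area. Section 3.2.1 would still conflict with itself.

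**Conclusion.** The point holds as a contradiction in the definition of the primary outcome, together with a small scoring error. *Local* is undefined and matches none of the three domains as described, nor the other sections that name the outcome. The site for B is tied neither to covered skin nor to the same place at both visits. The area weights total 104 instead of 100, an excess of at most 4 points of A, and only with hand involvement. Section 3.2.1 does not say how A, B and C are combined, so this excess cannot be carried through to the total score from the text shown.

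These conclusions rest on the wording and on addition, and do not depend on effect size, standard deviation or power. No loss of power is established: the lowest figures above are a worst case. Nor is whole-body scoring shown to be the wrong choice. This is something the sponsor should fix before patients are scored; it does not by itself invalidate the design.

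**What to change.** 1. **State one definition and use it in Sections 3.2.1, 7 and 8.2.** The scoring text as written supports whole-body SCORAD as primary. Delete *local*, and report a garment-area extent and intensity score as a secondary outcome from the same body drawing. If a local score is kept as primary instead, define the area, say how C is handled, and avoid percent change where the covered-skin baseline is near zero.
2. **Fix the site for B.** Record the representative site at Visit 1 and rescore the same site at Visit 2. The downside is small: that site may be less representative by Visit 2.
3. **Correct the weights.** State that palms and backs of hands count within the 9% for each upper limb, so that the total is 100%.

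The cost is wording and one added field on the SCORAD form, with no extra visit or procedure. The secondary garment-area score will carry little information for patients whose lesions are only on uncovered skin.

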## 8. Statistical Considerations

### 8.1 Study Hypotheses

The use of a textile coated with a natural biopolymer will improve clinical outcomes on patients with atopic dermatitis diminishing inflammatory biomarkers as well as the number of skin colonizing Staplylococcus aureus and expression of its virulence factors.

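### Section 3.2.1 names two unranked primary outcomes but section 8.2 sizes only SCORAD, so the protocol does not secure 5% error and 80% power together

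*Protocol*

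**What the plan says.** Protocol section 3.2.1 has a singular heading but two bullets at the same level. The first is investigator-rated severity: "Clinical improvement measured by local SCORAD", expressed as percentage change from the initial to the final assessment. The second is "Changes in Quality of life", collected at the start and end of the study with the "Portuguese version of the Dermatology Life Quality Index (> 16 years old") or, at ages 4 to 16, the corresponding children's index. Secondary outcomes follow separately in section 3.2.2, so quality of life has not been placed among them.

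Section 8.2 fixes a "significant level of 0.05" and a "statiscal power of 0.8" and then says that, "based on difference of means and standard deviation of outcome SCORAD the sample size calculated was 90 patients". It gives no numerical difference or standard deviation, and no calculation for quality of life.

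Section 8.1 says that the textile "will improve clinical outcomes on patients with atopic dermatitis", without naming either primary outcome. No section ranks the two or says whether success means one of them or both.

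**The concern.** Which outcomes are primary, and which outcome the sample size serves, are both settled in this protocol, and the two decisions do not match: two outcomes are primary and one is sized. Until they are aligned, the 0.05 and 0.8 in section 8.2 describe the SCORAD test but not necessarily the trial's conclusion. If a significant result on either outcome counted as success, the chance of a false claim would exceed 5%. If both had to be significant, the chance of success would fall below 80% even when the assumed effect is real. With unranked primaries, the choice between these readings could also be made after the results are known.

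**Working it through.** **Inputs from the protocol.** Two primary outcomes (section 3.2.1). Significance level 0.05, power 0.8, SCORAD as the basis, 90 patients (section 8.2).

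**Assumptions, because the protocol does not state them.** Two-sided tests; 1:1 allocation, so 45 per arm; no dropout; correlation r between the two test statistics from 0 to 0.9. For joint power, the same standardised effect on both outcomes.

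**Step 1: the plan's own figure.** With no difference or SD given, 90 cannot be reproduced forwards. Solved backwards:

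d = (1.960 + 0.842) × √(2/45) = 2.802 × 0.2108 = 0.591 SD

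The t-based version gives 0.597. So 90 patients give 80% power for one outcome at two-sided 0.05 if the true difference is about 0.59 SD.

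**Step 2: either outcome carries the claim, each tested at 0.05.** Family-wise error is 1 − P(|Z1| < 1.96 and |Z2| < 1.96) for bivariate normal statistics. At r = 0 this is 1 − 0.95² = 0.0975.

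**Step 3: both required, each tested at 0.05.** Each outcome has 80% power, so joint power is Φ₂(0.842, 0.842; r), where Φ₂ is the bivariate normal distribution function. At r = 0 this is 0.8² = 0.64. The last column is the total number of patients that restores 80% joint power at d = 0.591.

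| r | Error, either wins | Joint power, both required | Total N for 80% joint power |
|---|---|---|---|
| 0 | 9.75% | 64.0% | 120 |
| 0.3 | 9.5% | 66.6% | 116 |
| 0.5 | 9.1% | 68.7% | 114 |
| 0.7 | 8.4% | 71.3% | 108 |
| 0.9 | 7.0% | 75.0% | 102 |

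If quality of life has a smaller effect than SCORAD, joint power is lower. At r = 0.5 it is 58% for an effect of 0.5 SD and 44% for 0.4 SD.

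**Step 4: alpha split, 0.025 each.** The critical value rises from 1.960 to 2.241. SCORAD power at 45 per arm is Φ(2.802 − 2.241) = Φ(0.56) = 71%. To restore 80%, n per arm = 2 × (2.241 + 0.842)² / 0.591² ≈ 54.5, rounded up to 55, or 110 in total. The power to win on at least one outcome is 92%, 85% and 77% at r = 0, 0.5 and 0.9.

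**Step 5: SCORAD first at 0.05, quality of life only if SCORAD is significant.** A false claim on quality of life needs its own test to reject at 0.05, and nothing can be claimed unless the SCORAD test rejects at 0.05. Family-wise error therefore stays at 5%. SCORAD power stays at 80% with 90 patients. Success on quality of life now needs both tests to reject, so its power is the joint power in step 3.

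**The case against.** The strongest reply is that testing order, alpha allocation and success rules commonly sit in a statistical analysis plan, which is not shown here. That stands: the lack of a multiplicity method is not the defect. It does not remove the mismatch, because the protocol itself names the primary outcomes and states the basis of the sample size. A later plan could add a rule. It could not make 90 a number calculated for both outcomes, and demoting quality of life there would contradict section 3.2.1.

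A second reply is that no figure in section 8.2 is wrong. This also stands. A reader might infer that 5% error and 80% power cannot both hold. The documents do not support that: with SCORAD tested first, both hold at 90 patients, and under an equal split the power to win on at least one outcome exceeds 80% unless the correlation is high. Nor does the protocol claim 80% power for quality of life or for the two jointly. The 0.05 appears only in the sentence that sizes SCORAD, so it is an inference that quality of life shares it. It is likewise an inference that section 8.1 lets either outcome carry the claim, since that section gives a general hypothesis and not a decision rule.

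A reader might also infer that the adult and child questionnaires are pooled into one score. Section 3.2.1 only assigns a questionnaire by age; it does not say how the scores are analysed.

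Finally, near-doubling of the error belongs to low correlation. The patient-scored itch and sleeplessness in SCORAD make a positive correlation with quality of life plausible, which is why the range extends to r = 0.9.

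**Conclusion.** The point holds in conditional form. Two outcomes are labelled primary, one is sized, and they are not ranked, so the protocol does not secure 5% error and 80% power together. What fails depends on the rule eventually applied: error rises to between 7.0% and 9.75% if either outcome suffices; joint power is 64% to 75% if both are required; SCORAD power is 71% if alpha is split equally.

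The sizes rest on two-sided tests, 1:1 allocation and no dropout. The error range needs no effect size. The joint-power range needs each outcome to have 80% power, which for quality of life is an assumption without support in the protocol. The 0.59 SD is back-solved and is not a figure the protocol states.

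**What to change.** In section 3.2.1, keep SCORAD change from baseline to the final visit, defined as it is now, as the sole primary outcome. Move quality of life to the head of section 3.2.2 as the first secondary outcome, and add one sentence saying that it is formally tested at 0.05 only if the SCORAD result is significant. The definition of the SCORAD outcome should not be altered as part of this change. No additional patients, visits or data are needed, and 5% error and 80% SCORAD power both hold at 90 patients under the assumptions above.

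The cost is that quality of life can no longer support a confirmatory claim when SCORAD is not significant. If the sponsor wants both outcomes to remain primary, the alternative is to state the success rule and size for it. Under the same assumptions that means about 102 to 120 patients if both are required, or about 110 to keep 80% SCORAD power under an equal alpha split.
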